| Research steps | The present study inlcuded 2 weeks washout period and 8 weeks double-blind randomized treatment period. Interview is needed after treatment for 2 weeks, 4 weeks and 8 weeks. After finishing the double blind randomized treatment period, there is a safety observation period of 56 weeks. There is an interview every 8 weeks.  All the subjects signed the informed consent prior to screening.  Screening/cleaning periods (Interview 1, -3 ~ 0 week)  The starting of giving the treatment with the research drug in the first 3 weeks, and before taking placebo (that is -3 weeks to -2 weeks), the following screening assessment projects should be finished:   - Demographic data including gender and age (date of birth) of the subjects; - Height, weight, waist circumference, smoking and drinking status; - Collecting of the disease history: inquire and record the history of hypertensive disease of the subjects (including the time of illness of hypertension and levels of blood pressure), family history, complications/disease and treatment history, other previous disease and treatment history, allergic history; - Physical examination: conducting of the physical examination of all body systems; - Resting seated blood pressure and measurements of heart rate; - Laboratory and auxiliary examinations: including urine pregnancy test (limited to women of childbearing age), whole blood test, urine routine test test, liver function, kidney function, fasting blood glucose, blood lipid, blood electrolyte and a 12-lead electrocardiogram.   For the patients preliminarily screened as the medium and low risk primary hypertension basically meeting the inclusion criteria but not meeting the exclusion criteria, they entered the placebo washout period of 2 weeks (-2 ~ 0 weeks). The patients will provide and take placebo for 2 weeks. At the same time, diary cards will be given.  In addition, the adverse events and concomitant treatments will be recorded between the signing of the informed consent and taking placebo for 2 weeks.  Baseline (Interview 2, 0 week)  After the subjects took the placebo for 2 weeks, the following aspects should be conducted:   - Measurement of the resting sitting blood pressure and heart rate: the measurement method was as the same as that of the screening period; - Auditing the inclusion/exclusion criteria, the qualified candidates were given random numbers (i.e. drug numbers) according to the order of entering groups from small to large; - According to the random number, the research drugs for the first ~ second week treatment period were provided (including alternative medicine of 3 days); - Recovery of the research drugs of 2 weeks in the placebo washout period; - Transfering and recording of the diary card of subjects; - Recording adverse events and concomitant treatments.   The treatment period (Interview 3, 2 weeks ± 3 days)   - After the subjects taking the research drugs in the double-blind randomized treatment period for 2 weeks, the following aspects were needed to be carried out: - Measurment of the resting sitting blood pressure and heart rate: the measurement method was as the same as that of the screening period; - According to the random number, the research drugs for the third ~ fourth week treatment period were provided (including alternative medicine of 3 days); - Recovery and counting of the remainder research drugs in the first and second week; - Transfering and recording of the diary card of the subjects;   Recording adverse events and concomitant treatments.  The treatment period (Interview 4, 4 weeks ± 3 days)   - After the subjects taking the research drugs in the 4 weeks double-blind randomized treatment period, the following aspects were needed: - Measurement of the resting sitting blood pressure and heart rate: the measurement method was as the same as that of the screening period; - Laboratory examinations: urine routine test, liver function, renal function and serum electrolyte; - The research drugs of the treatment period between the fifth week and the eighth week were distributed according to the random number (including the reserve drug for 6 days); - Recovery and counting of the remainder research drugs in the third and fourth week; - Transfering and recording of the diary card of the subjects; - Recording adverse events and concomitant treatments.   Finishing of the random treatment (Interview 5, 8 weeks ± 3 days)  After the subjects taking the research drugs in the double-blind randomized treatment period for 8 weeks, the following aspects were needed to be carried out:   - Physical examination: physical examination of all body systems was conducted including body weight; - Measurements of the resting sitting blood pressure and heart rate: the measurement method was as the same as that of the screening period; - Laboratory and auxiliary examinations: including urine pregnancy test (only limited to women of childbearing age), whole blood test, urine routine test, liver function, renal function, fasting blood glucose, blood lipid, blood electrolyte and a 12-lead electrocardiogram. - Recovery and counting of the remaining research drugs of the fifth ~ eighth week; - Distribution of Allisartan Isoproxil tablets for 9 weeks’ dose; - Recovery, transfer and recording the diary cards of the subjects; - Recording of the adverse events and concomitant treatments.   Safety observation period (Interview 6-11, 9-56 weeks, one interview for every 8 weeks, the window period ±7 days)  In order to observe the long-term efficacy and safety of the research drugs, all the subjects participated in the research of the safety observation period of 56 weeks on a voluntary basis after they finished the double-blind randomized study of 8 weeks, during which every subject would accept one treatment of 240 mg Allisartan Isoproxi tablet daily. The subjects should visit the research doctor every 8 weeks:   - Measurement of resting sitting blood pressure and heart rate: the measurement method was as the same as that of the screening period; - Laboratory examination was conducted when it was necessary: urine routine test test, liver function, renal function and serum electrolyte; - Allisartan Isoproxil tablets for 9 weeks dose was distributed; - Recoveryand counting of the remainer research drugs of the past 8 weeks; - Transfer and recording of the diary card of subjects; - Recording of the adverse events and concomitant treatments.   In the review 9, namely the review in which the subjects took the research drugs for 32 weeks of the observation period, in addition to the above items, the following aspects were also needed:   - Physical examination: conducting physical examination of all body systems including weight; - Laboratory and auxiliary examinations: including whole blood test, fasting blood glucose, blood lipid, blood electrolyte and a 12-lead electrocardiogram.   After finishing the safety observation period (review 12, the sixty-fourth week ±7 days.)  After finishing the observation period of 56 weeks of treatment for the participants, the following aspects were needed:   - Physical examinations: physical examination of all body systems including body weight; - Measurement of the resting sitting blood pressure and heart rate: the measurement method was as the same as that of the screening period; - Laboratory and auxiliary examinations: including urine pregnancy test (only limited to women of childbearing age), whole blood test, urine routine test, liver function, renal function, fasting blood glucose, blood lipid, blood electrolyte and a 12-lead electrocardiogram. - Recovery and counting of the remaining research drug of the fifty-seventh ~ sixty-fourth week; - Transfer and recording of the diary cards of subjects; - Recording adverse events and concomitant treatment.   Unplanned interview (when the research required or exiting test in advance)  If subjects needed extra interviews or exiting test in advance, the measures that researchers have taken (including the results of laboratory tests) should be recorded on the original records and the unplanned review table in the case report table.  In addition, when the subjects exited tests in advance before the interview 5 or after they entered the safety observation period and ended early safety observation period, the following aspects should be conducted as far as possible:   - Physical examination: physical examination of all body systems; - Measurement of the resting sitting blood pressure and heart rate: the measurement method was as the same as that of the screening period; - Laboratory and auxiliary examination: including urine pregnancy test (only limited to women of childbearing age), whole blood test, urine routine test test, liver function, renal function, fasting blood glucose, blood lipid, blood electrolyte and a 12-lead electrocardiogram; - Recovery and counting of all the remaining research drugs; - Recovery, transfer and recording of the diary cards of subjects (only applicable to the subjects during the double-blind research period); - Recording adverse events and concomitant treatment. |

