
**Experimental flow chart**

|  | **Screening and cleaning periods** | | | **Baseline period** | **The treatment period (window period ± 3 days)** | | | **Safety observation period 5 (window period ± 7 days)** | | | |
| --- | --- | --- | --- | --- | --- | --- | --- | --- | --- | --- | --- |
| **Screenig** | | **Cleaning** |
| Interview times | **1** | | | **2** | **3** | **4** | **5** | **6-8** | **9** | **10-11** | **12** |
| Interview time (week) | **－3～－2** | **－2～0** | | **0** | **2** | **4** | **8** | **9-32** | **40** | **48-56** | **64** |
| Signing written informed consent | **X** |  | |  |  |  |  |  |  |  |  |
| Collecting Medical History | **X** |  | |  |  |  |  |  |  |  |  |
| Physical examination | **X** |  | |  |  |  | **X** | **X6** | **X** | **X6** | **X** |
| Blood pressure and heart rate in sitting position | **X** |  | | **X** | **X** | **X** | **X** | **X** | **X** | **X** | **X** |
| Auditing inclusion/exclusion criteria | **X** |  | | **X** |  |  |  |  |  |  |  |
| Urine pregnancy test 1 | **X** |  | |  |  |  | **X** |  |  |  | **X** |
| Routine blood test 2 | **X** |  | |  |  |  | **X** | **X6** | **X** | **X6** | **X** |
| Routine urine test 3 | **X** |  | |  |  | **X** | **X** | **X6** | **X** | **X6** | **X** |
| Liver function（ALT、AST、  TBil） | **X** |  | |  |  | **X** | **X** | **X6** | **X** | **X6** | **X** |
| Renal function（Bun、Cr、  Ua） | **X** |  | |  |  | **X** | **X** | **X6** | **X** | **X6** | **X** |
| Blood fat（TG、TC、HDL、LDL） | **X** |  | |  |  |  | **X** | **X6** | **X** | **X6** | **X** |
| Fasting blood-glucose（FPG） | **X** |  | |  |  |  | **X** | **X6** | **X** | **X6** | **X** |
| Blood electrolytes（K、Na、  Cl） | **X** |  | |  |  | **X** | **X** | **X6** | **X** | **X6** | **X** |
| 12 electrocardiograph（ECG） | **X** |  | |  |  |  | **X** |  | **X** |  | **X** |
| The drug release of the cleaning period 4 | **X** |  | |  |  |  |  |  |  |  |  |
| The drug recovery of the cleaning period |  |  | | **X**4 |  |  |  |  |  |  |  |
| 收Release and recovery of the research drugs |  |  | | **X** | **X** | **X** | **X** |  |  |  |  |
| Drug release and recovery of the safety observation period |  |  | |  |  |  | **X** | **X** | **X** | **X** | **X** |
| Release, recovery and transcription of diary cards of the subjects | **X** | **X** | | **X** | **X** | **X** | **X** |  |  |  |  |
| Recording concomitant medication | **X** | **X** | | **X** | **X** | **X** | **X** | **X** | **X** | **X** | **X** |

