| Recording adverse events | **X** | **X** | | **X** | **X** | **X** | **X** | **X** | **X** | **X** | **X** |

1. It applies only to women of childbearing age.

2. Whole blood test indexes include the following aspects: total numbers of erythrocytes and leukocytes, and percentages of neutrophile granulocytes and lymphocytes, platelet count, hemoglobin and hematocrit.

3. The indexes of routine urine detection inlcude the following aspects: urine leukocytes, urine erythrocytes and urine proteins and carbohydrate.

4. The released drugs of the cleaning period can meet applciation for 17 days. The cleaning period was 14 days. The participants must be back to the hospital in 14 ± 3 days for baseline interview.

5. Interview was conducted once every 8 weeks, and a total of 7 interviews were carried out.

6. If there is abnormity of the laboratory examinations in the previous double-blind period, reexamination must be conducted. If it is normal in the previous results, the researchers can decide whether to inspect according to their own circumstances;

Note: according to the conditions of the patients, the researchers can increase the safety inspection of the subjects at any time.

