**3）Regulations of breaking blinding**

At the same time of encoding the research drugs, an emergency message was prepared for each drug number by the biostatisticians producing blinding end. The exact group of the number of the drug was sealed in the letter envelope. The emergency letters accompanied with the drugs of the corresponding numbers were distributed to various clinical research units by the researchers in charge of the unit. Emergency letter can only be used for emergency. They will be unsealed only the medication conditions should be understood and the treatment measures should be taken such as serious adverse events.

If the emergency envelope is opened, the exposing blind time, date and the reasons must be recorded on the envelope and the name of the people uncovering the blind should be signed off, and the Hangzhou Tigermed Co. Ltd. (CRO) company should be informed immediately. Once emergency letter is opened, the case is treated as the shedding case.

At the end of the study, all the emergency letters (opened or not) must be called back together with the completed case report form. The emergency letters should be checked when inspector visits each time to determine the envelope is not opened freely, or the number of envelops that have been opened is recorded clearly.

Blind can not be broken after double-blind treatment of 8 weeks. All participants will take part in a safety observation period of 56 weeks under blind states. The time of blind exposure is determined according to the requirements of the data statistics and analysis procedures of the double-blind treatments.

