### The safety observation period (Interview 6-11, 9-56 weeks, every interview for 8 weeks, the window period ± 7 days)

In order to observe the long-term efficacy and safety of the research drugs, all the subjects would participate in the safety observation period research of 56 weeks voluntarily after they finish the double-blind randomized study of 8 weeks, during which each subject will receive 240 mg Allisartan Isoproxil tablet treatment once a day, and the subjects should visit the doctor every 8 weeks:

- - Resting sitting blood pressure and heart rate were measured: the measurement method is the same as that of the screening period;
  - Laboratory examinations: urine routine test test, liver function, renal function and serum electrolyte (if the laboratory indicators are abnormal in the observation of former 8 weeks, please reexamine; if it is normal, please judge freely whether reexamination is necessary according to the circumstances);
  - Distribution of Allisartan Isoproxil tablets for 9 weeks doses;
  - Residual drug recovery of the past 8 weeks and counting;
  - Recovery, transfer and recording of the diary cards of the subjects;
  - Recording adverse events and concomitant treatments.

The interview 9, namely the interview of the subjects taking the research drugs for 32 weeks during the safety observation period, in addition to the above items, the following aspects are also needed to be conducted:

- - Physical examination: physical examination of all body systems including weight;
  - Laboratory examinations: urine routine test test, liver function, renal function and serum electrolyte;
  - Laboratory and auxiliary examinations including whole blood test, fasting blood glucose, blood lipid, blood electrolyte and a 12-lead electrocardiogram.

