## Medication methods

**The double-blind treatment period**

Test group: Allisartan Isoproxil tablet 240 mg, 1 time a day, oral administration of half an hour before breakfast fasting for 8 weeks.

Control group: Allisartan Isoproxil placebo tablet 240mg, 1 time a day, oral administration of half an hour before breakfast fasting for 8 weeks.

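### Normal results on placebo can excuse laboratory tests after the switch to 240 mg, so former placebo patients may have no required on-drug renal, liver, urine or electrolyte test until week 40

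*Protocol*

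**What the plan says.** After eight weeks of double-blind treatment, patients may enter a voluntary 56-week safety observation period in which everyone takes allisartan 240 mg daily. Interviews 6 to 12 follow at 8-week intervals.

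- **Flow chart.** Urine, liver function, renal function and electrolytes carry note 6 at Interviews 6-8 and 10-11. They carry an unconditional mark only at Interview 9 (week 40) and Interview 12 (week 64).
- **Note 6.** An abnormal double-blind result must be re-examined. For a normal one, "If it is normal in the previous results, the researchers can decide whether to inspect according to their own circumstances".
- **Section 5.3.6.** The four panels are listed for the 8-weekly visits with a similar discretion: "if it is normal, please judge freely whether reexamination is necessary according to the circumstances". For Interview 9 it lists all four without a condition and describes that visit as "namely the interview of the subjects taking the research drugs for 32 weeks during the safety observation period".
- **Section 6.2.** "Control group: Allisartan Isoproxil placebo tablet 240mg, 1 time a day, oral administration of half an hour before breakfast fasting for 8 weeks".
- **Section 9.1.2.** It gives renal toxicity in animals as a reason for testing these four panels. In poorly translated wording, it appears to intend testing at week 4 and then every 8 weeks in the safety period.
- **Protocol summary, research steps.** For the 8-weekly visits: "Laboratory examination was conducted when it was necessary: urine routine test test, liver function, renal function and serum electrolyte". The additional list for Interview 9 reads "Laboratory and auxiliary examinations: including whole blood test, fasting blood glucose, blood lipid, blood electrolyte and a 12-lead electrocardiogram", so of the four panels it names only electrolytes.

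Neither note 6 nor section 5.3.6 distinguishes patients by what they took in the double-blind period.

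**The concern.** A waiver based on earlier normal results makes sense for test-arm patients, who by week 8 have been tested twice on 240 mg. It does not carry over to the control arm. Those patients' week-4 and week-8 results were obtained on placebo, and they are new to the drug when the safety period begins.

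The protocol's own standard for newly exposed patients is visible in the test arm: the four panels at weeks 4 and 8 on drug, required of everyone. Former placebo patients are equally new to 240 mg, yet nothing obliges anyone to test them until much later, and no reason is given for the difference.

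What is at stake is patient safety, not the randomised comparison. A symptomless rise in creatinine, transaminases or potassium in a former placebo patient would be found before week 40 only if the investigator chose to test. Blood pressure readings and adverse-event questions would not reveal it.

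**Working it through.** **Visit dates.** Active drug starts for the control arm at Interview 5, week 8, and visits follow every 8 weeks. The flow chart gives the status of the four panels.

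| Interview | Week | Weeks on 240 mg, former placebo arm | Urine, liver, renal, electrolytes |
|---|---|---|---|
| 5 | 8 | 0 | required, but off drug |
| 6 | 16 | 8 | discretionary if earlier results normal |
| 7 | 24 | 16 | discretionary |
| 8 | 32 | 24 | discretionary |
| 9 | 40 | 32 | required |
| 10, 11 | 48, 56 | 40, 48 | discretionary |
| 12 | 64 | 56 | required |

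This reproduces the protocol's own figures: seven safety visits (flow chart, note 5), and 40 − 8 = 32 weeks on drug at Interview 9 (section 5.3.6).

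**Longest wait, with windows.** Interview 5 has a window of ±3 days and Interview 9 of ±7 days.

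- Nominal: 280 − 56 = 224 days.
- Shortest: (280 − 7) − (56 + 3) = 214 days.
- Longest: (280 + 7) − (56 − 3) = 234 days.

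**Test arm, for comparison.** The first required on-drug set is at week 4: 28 ± 3 days, or 25 to 31 days. The nominal ratio is 224 / 28 = 8.

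**Does the wording of the waiver matter?** Note 6 refers to the double-blind period. Section 5.3.6 refers to the former 8 weeks, which could mean the latest interval instead. No test is scheduled between Interview 5 and Interview 6, so on either reading the results that justify skipping Interview 6 are placebo results for this arm. If Interview 6 is skipped, no on-drug result exists to compel a test at Interview 7, and the same holds at Interview 8.

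**Patients affected.** These are former placebo patients who enter the voluntary period with normal results. The protocol randomises 130 per arm, assumes 20% loss and plans 108 evaluable per arm.

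- 20% loss applied to 130: 130 × 0.8 = 104.
- Planned evaluable: 108.
- Ceiling, with no loss: 130.

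Uptake and the share with normal results are not stated. If, as an assumption, only 50% entered and 70% of those were normal, the figure would be 104 × 0.5 × 0.7 ≈ 36.

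**With the four panels required at Interview 6.** The wait is 112 − 56 = 56 days (46 to 66 with windows), or 8 weeks instead of 32.

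**The case against.** The strongest reply is that nothing is waived automatically and the hazard is small. Investigators decide case by case, know that every patient now takes 240 mg, and may add safety tests at any time. Section 4.2 excludes renal insufficiency, renal artery stenosis, serious liver disease and potassium or sodium abnormality. Section 7.2 prohibits potassium supplements, potassium-sparing diuretics and indometacin. Section 5.3.8 asks for these tests, as far as possible, in anyone who leaves early. The background section names the kidney as the target organ in rats, but toxicity arose at 80 mg/kg/day, 20 mg/kg/day was non-toxic, and the tubular change is described as a common spontaneous lesion. In the earlier phase II trial, creatinine fell on 240 mg, liver indices did not change significantly, and the week-4 potassium rise on 240 mg was not reported at week 8.

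All of this stands and makes the hazard modest. None of it guarantees that a newly exposed patient is tested before week 40.

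Four stronger readings are tempting, and the document does not support them.

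- **That section 9.1.2 flatly contradicts note 6.** Its sentence is garbled. It may state the general schedule that note 6 and section 5.3.6 then qualify. It needs aligning; a contradiction is not established.
- **That the first required renal and liver test is week 64.** This needs the summary's Interview 9 list read alone. The flow chart and section 5.3.6 both require those tests at week 40. The summary list is incomplete.
- **That investigators stay blind throughout and so cannot know who is newly exposed.** Section 5.2.2 does say "All participants will take part in a safety observation period of 56 weeks under blind states", but then ties unblinding to the analysis of the double-blind phase, which section 3 plans for December 2009. Taking enrolment as 1 May to 31 August 2009, Interview 6 (+112 days) falls between 21 August and 21 December 2009, and Interview 9 (+280 days) between 5 February and 7 June 2010. Investigators may not know at Interview 6; more cannot be said.
- **That 104 patients is a maximum.** The protocol plans 108 evaluable per arm and randomises 130.

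**Conclusion.** The point holds. Under the flow chart, note 6 and section 5.3.6, a former placebo patient with normal results can go 32 weeks on 240 mg (214 to 234 days) before the first required urine, liver, renal and electrolyte tests, against 4 weeks in the test arm. This is the longest wait the text permits, not a prediction of what sites would do.

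About 104 to 108 patients are affected if 20% are lost and all others continue with normal results, with a ceiling of 130. The true number depends on uptake and on the share with normal results, neither of which is stated. Two smaller drafting faults go with it: the incomplete Interview 9 list in the summary and the unclear sentence in section 9.1.2. Given the modest hazard, this is a cheap improvement that should be made.

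**What to change.** In note 6, section 5.3.6, section 9.1.2 and the summary, write to this effect:

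> At Interview 6, urine routine, liver function, renal function and blood electrolytes are tested in every patient, whatever the double-blind results. At Interviews 7, 8, 10 and 11, each of these four panels may be waived only after a normal result for that panel obtained on allisartan in the safety observation period. Abnormal double-blind results must still be re-examined.

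Add urine, liver and renal tests to the summary's Interview 9 list so that it matches the flow chart and section 5.3.6. Applying the Interview 6 rule to both arms means no one has to be unblinded. The other items marked with note 6 can stay as they are.

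The cost is wording plus one set of four routine panels per patient at a visit already scheduled: 260 × 0.8 = 208 sets, or 216 on the planned evaluable number, at full uptake, with a ceiling of 260. About half would fall on test-arm patients already tested on drug at weeks 4 and 8. The net addition is smaller, because patients with abnormal double-blind results must be retested anyway and some investigators would have tested. The wait falls to 8 weeks, still longer than the test arm's 4.
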